## Materials and methods

### Study design

This study design adheres to a randomized, sham-controlled, single-center clinical trial, in accordance with the Standard Protocol Items Recommendations for Intervention Trails (SPIRIT) guideline (Chan et al., 2015). The study will be conducted in the Department of Rehabilitation Medicine at The First Affiliated Hospital of Sun Yat-sen University, China. The research protocol was approved by the Ethics Committee of FAH-SYSU (No. [2020]471). The trial was prospectively registered on www.chictr.org.cn under the registration number ChiCTR2100050543.

Patients will be randomly assigned to one of two groups: an experimental group (EG) and a control group (CG). While all participants will receive routine SLT, the EG will also receive real TMS while the CG will receive sham TMS. The intervention consists of 10 sessions over 2 weeks. The outcomes will be measured at three time points: baseline (T0), 3–5 days before the first session; post-intervention (T1), 3–5 days after the last session; and follow-up (T2), 12 weeks after the last session. The flow chart of this study protocol is shown in Figure 1.

**FIGURE 1 F1:**
[figure not shown]
Flow chart of the present study protocol. EG, experimental group; CG, control group; Cb, cerebellum; cTBS, continuous theta burst stimulation; SPL, sound pressure level; MPT, maximum phonation time; ERP, event-related potential; rs-fMRI, resting-state functional magnetic resonance imaging; GRBAS, grade, rough, breathiness, asthenia and strain; SCWT, Stroop Color and Word Test; QoL, quality of life.

### Participants

#### Inclusion criteria

We will recruit patients who meet the following criteria: (a) diagnosed with idiopathic PD by a neurologist according to the UK Parkinson’s disease Society Brain Bank (Hughes et al., 1992); (b) aged 50–80 years; (c) right-handedness; (d) Mandarin as their primary language; (e) normal hearing function; (f) Modified Hoehn & Yahr (mH&Y) scale of 1.5–3; (g) Mini-Mental State Examination (MMSE) score ≥ 26; (h) no previous speech therapy; and (i) stable dopaminergic medication assessed by Levodopa Equivalent Daily Dose (LEDD) for a minimum of 4 weeks preceding baseline assessment.

#### Exclusion criteria

We will exclude patients who have any of the following conditions: (a) contraindications for MRI and TMS (e.g., claustrophobia, cardiac pacemaker); (b) focal neurological disorders (e.g., epilepsy, stroke, brain injury or tumor) or related psychiatric disorders; (c) history of brain surgery such as deep brain stimulation; or (d) unstable medical conditions.

#### Sample size

To date, none of studies has investigated the effects of cerebellar cTBS on speech impairment in patients with PD. However, our previous study reported positive effects of cerebellar cTBS on impaired auditory-vocal integration in patients with SCA (Lin et al., 2022), who similarly showed abnormally enhanced vocal compensations for pitch perturbations (Li et al., 2019). Based on the obtained partial η^2^ value of 0.559 in that study, we performed an estimation of effect size using G*Power software (version 3.1). Specifically, we used *a priori* F-tests for repeated-measures within-between interaction to determine the required sample size for our study. Our calculations indicated that a total sample size of 16 participants would be necessary to achieve a power of 0.95 and an alpha level of 0.05, considering the presence of two groups. The chosen sample size allows us to adequately investigate the research question while considering resource constraints. To account for potential dropouts and data quality issues, we increased the sample size by 20%, resulting in a final sample size of at least 10 participants per group. However, it is important to note that this sample size calculation is based on the immediate aftereffects of cerebellar cTBS on speech impairments in patients with SCA. Therefore, this study protocol will recruit a total of 40 participants, with 20 participants allocated to each group, for a more conservative approach.

### Randomization, allocation, and blinding

We will use block randomization with a block size of 4 and a 1:1 allocation ratio to assign patients with PD who pass the screening to either the experimental or control group. Randomization will be stratified by gender and age. An independent statistician, who is not be involved in participant enrollment, assessment, or intervention, will generate the randomization sequence. Allocation concealment will be ensured using sealed opaque envelopes, and each envelope will bear a serial number on the outside and a group number on the inside. After baseline assessments, an independent research assistant will open the envelopes in order and assign participants to one of the two groups based on the group number enclosed. Participants, outcome assessors, and data analysts will be blinded to the allocation and intervention.

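### A single stated block size of 4, at one site with a coil operator who must know the arm, leaves about 25% to 33% of allocations deducible by anyone tracking them; varying, undisclosed block sizes would remove most of that certainty

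*Protocol article*

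**What the plan says.** The section on randomization, allocation and blinding fixes one block size: "We will use block randomization with a block size of 4 and a 1:1 allocation ratio". It adds: "Randomization will be stratified by gender and age". No age cut-point or number of strata is given.

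The same section describes several safeguards:
- The sequence comes from an independent statistician "who is not be involved in participant enrollment, assessment, or intervention, will generate the randomization sequence".
- Envelopes are sealed and opaque; on their labelling: "each envelope will bear a serial number on the outside and a group number on the inside".
- On when and by whom they are opened: "After baseline assessments, an independent research assistant will open the envelopes in order".
- On blinding: "Participants, outcome assessors, and data analysts will be blinded to the allocation and intervention". Coil operators and recruiting staff are not in that list.

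Two other places bear on the point. Under Study design the trial is single-centre: "The study will be conducted in the Department of Rehabilitation Medicine" of one hospital. Under Transcranial magnetic stimulation, sham uses the same parameters but with the coil turned through 90° so that only its edge touches the scalp. The Sample size section sets recruitment at 40, with 20 per group.

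**The concern.** In a 2:2 block of four, the fourth allocation is always fixed by the first three, and the third is fixed whenever the first two agree. A block size that is constant and stated lets anyone who sees past allocations count off the rest of the block.

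Here at least one person sees them. The sham method means the operator cannot be blind, and with one department every allocation in a stratum takes place in the same setting. The article does not say that operators are kept apart from screening and enrolment.

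The decision at risk comes before the envelope is opened: whom to approach, whom to screen, and when to bring a patient in. If someone who can foresee the next arm influences that decision, patients can be steered by, for example, speech severity. Sealed envelopes do not prevent that kind of selection bias. With 20 patients per arm, a few steered entries could shift baseline severity between the arms.

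**Working it through.** The article gives no figure for predictability, so there is none to reproduce.

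**Inputs from the article.** Block size 4, ratio 1:1, stratification by gender and age (Randomization section); 40 patients (Sample size section); one site (Study design).

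**Assumptions.** The article gives no number of strata, so a range of 2 to 8 is shown, with patients falling at random into equally likely strata. The observer knows the block size, the stratum and every earlier allocation in the block.

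**Step 1: complete blocks.** There are 4!/(2!·2!) = 6 possible blocks, hence 24 allocations. Chance that each position is certain:
- positions 1 and 2: 0
- position 3: P(first two agree) = 2/6 = 1/3
- position 4: 1

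Share certain = (0 + 0 + 1/3 + 1)/4 = 1/3, that is 8 of 24. For 40 patients in complete blocks: 40 × 1/3 = 13.3.

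**Step 2: best-guess accuracy.** Always guessing the arm that is behind is right with probability 1/2, 2/3, 2/3 and 1 at the four positions: (1/2 + 2/3 + 2/3 + 1)/4 = 0.708, against 0.5 for a coin toss.

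**Step 3: incomplete blocks in strata.** The certain positions come late in a block, so an unfinished last block lowers the share. A stratum of 10 has two complete blocks (2 × 4/3 = 2.67 certain) plus two early positions (0 certain): 2.67/10 = 26.7%. With 40 patients split at random over equal strata (20,000 simulations):

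| Assumed strata | Certain, of 40 | Share |
|---|---|---|
| 2 | 12.5 | 31.2% |
| 4 | 11.7 | 29.2% |
| 6 | 10.8 | 27.1% |
| 8 | 10.0 | 25.0% |

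Four unequal strata (36%, 24%, 24%, 16%) also give 29.2%. One third is therefore the upper end for the stratified design.

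**Step 4: effect of mixing sizes 4 and 6 at random.** The same full-history yardstick is used. The observer knows that sizes are 4 or 6 with equal chance but not where blocks begin, and updates the probabilities after each allocation. An allocation counts as certain when its probability is 0 or 1.

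| Sequence length | Fixed 4, certain | Mixed 4/6, certain | Fixed 4, best guess | Mixed 4/6, best guess |
|---|---|---|---|---|
| 40 | 33% | about 6% | 71% | 69% |
| 10 | 27% | about 6% | 68% | 68% |

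The gain is the loss of certainty. The average quality of a guess hardly changes.

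**The case against.** Fixed small blocks are common and are not an error or a contradiction. The article's safeguards are real: a statistician outside enrolment, assessment and intervention, opaque numbered envelopes, an independent assistant to open them, and opening only after baseline. Table 1 places screening and consent before allocation, so a patient is already committed when the envelope is opened. Nothing says that the operator recruits or passes allocations on, and no bias is shown; only guessability is computed. All of this stands, and it keeps the point modest. It does not dispose of it: the safeguards hide the next envelope but not the arithmetic of the previous ones, and someone who can foresee the arm may still influence whom to approach and when.

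Two stronger readings are tempting and fail:
- A reader might infer that the design makes a third of allocations certain. That figure needs complete blocks and an observer with full history; under the stratification described, the share is lower.
- A reader might infer from the instruction that "an independent research assistant will open the envelopes in order and assign participants" that there is one envelope series, which would ignore gender and age and so defeat the stratification. The article does not say there is only one series. Numbered envelopes opened in order fit a separate series per stratum equally well, and stratum labelling is a detail that an article may leave to the full protocol.

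**Conclusion.** The concern holds in limited form. With one stated block size of 4, a single site and an operator who necessarily knows the arm, an observer with full within-block history could deduce up to 33% of allocations. The share is about 25% to 31% with 8 to 2 assumed strata. Across these cases that is roughly 10 to 13 of 40 patients.

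The figures measure opportunity, not bias. They rest on the observer knowing the block size, stratum and earlier allocations, and they matter only if that person affects whether or when patients enter. That the operator knows the arm is inferred from the sham method; the article does not say it in words. No finding is made on how the envelopes implement the strata. The point is a cheap improvement.

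**What to change.** For patients still to be randomised:

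1. The independent statistician prepares the remaining sequence with randomly varying block sizes, for example 4 and 6.
2. The sizes are not disclosed to anyone who screens, enrols or treats.
3. The protocol states that coil operators take no part in screening or enrolment.

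The cost is a new list and envelopes from the statistician already in place, and a short amendment. No treatment, outcome or sample size changes. The one downside is slightly more arm imbalance where strata end in incomplete blocks: an unfinished block of 4 leaves a stratum at most 2 patients apart, an unfinished block of 6 at most 3. The final split may therefore sit a little further from 20/20.

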### Intervention

All participants will receive routine SLT and 10 sessions of TMS intervention (real or sham cerebellar cTBS) over 2 weeks. The SLT will consist of 30 min of group speech therapy delivered by speech-language pathologists (SLPs), with four patients per group. The SLT will aim to improve voice/speech quality through exercises involving breathing control, vowel vocalization, reading, and singing. Notably, the SLPs will personalize the training materials based on the family background and interests of patients with PD and adjust the program during training according to individual conditions. The administration of cerebellar cTBS will precede the SLT. All interventions will be conducted at the same time of day when the patients are in their “ON” state, and their medication will be kept constant throughout the trial.

### Transcranial magnetic stimulation

Cerebellar cTBS will be administered using a magnetic stimulator (YIRUIDE CCY-1, Wuhan, China) with a 70 mm figure-of-8 coil. Neuronavigation software (Visor 2.0, ANT Neuro, Netherlands) in conjunction with a motion tracking system (Polaris Spectra, NDI, Canada) to ensure accurate and consistent coil positioning over the target areas. Before stimulation, we will measure the active motor threshold (AMT) from the right first dorsal interosseous muscle (FDI) by applying single-pulse TMS over the left M1 for each participant. The AMT is defined as the minimum stimulation intensity required to elicit motor-evoked potentials (MEPs) > 200 μv in tonically contracted muscles (10% of maximum contraction) in at least 5 out of 10 consecutive trials. A standard cTBS protocol that consists of 600 pulses in a theta burst pattern (bursts of 3 pulses at 50 Hz repeated every 200 ms) (Huang et al., 2005) will be delivered at 80% of AMT.

The VII lobe of the right cerebellum will be targeted as a stimulation site, as previous research has shown improved auditory-vocal integration in patients with SCA when cTBS was applied over this region (Lin et al., 2022). The mean Montreal Neurological Institute (MNI) coordinates are (42, -56, -30) (Stoodley, 2012). Structural MRI data from each participant will be imported into the neuronavigation software and segmented to obtain a realistic head model of the scalp and brain. During the navigation, the coil will be placed tangentially to the scalp and adjusted to reach the target markers. The neuronavigation software will provide distance and angle values as figures of merit for targeting. When the distance and angle between the coil and target are below predefined thresholds (distance < 2 mm, angle < 10°), the values will turn green to indicate the desired targeting precision. For the sham group, the same experimental parameters will be used except that the coil will be tilted at 90° with only the edge touching the scalp. This sham procedure ensures similar noise and scalp sensation but does not induce cortical activation.

### Outcome assessment

A comprehensive range of behavioral, neurophysiological, and neuroimaging measures will be used to investigate the effects of cerebellar cTBS on speech functions in patients with PD. In addition, other measures such as cognitive function and quality of life will also be assessed. All outcome measures will be collected at pre-intervention, post-intervention and follow-up assessments, with data acquired in the “ON” medication state at each time point. To ensure that patients with PD remain in the ON medication state throughout the experiment, clear instructions will be provided to them to adhere to their regular medication schedule for the duration of the study. And we will prioritize assessments involving voice/speech function and the FAF paradigm, followed by the assessment of cognitive function and questionnaires. These evaluations will take between 60 to 90 min, a timeframe that fits within the effective period of levodopa. Table 1 provides an overview of all measures and their corresponding time points.

**TABLE 1 T1:** Schedule of recruitment, intervention and assessment.

	Study period				
	Enrollment/Baseline	Allocation	Post-allocation		
Timepoint	W-1	0	W1	W2	W14
**Enrolment**					
Eligibility screen	X				
Informed consent	X				
Randomization	X				
Allocation		X			
**Intervention**					
Real cTBS + rehabilitation					
Sham cTBS + rehabilitation					
**Assessments**					
**Basic characteristics**					
Demographic characteristics	X				
Medical history	X			X	X
Modified H&Y stage	X			X	X
MMSE	X			X	X
Hearing test	X			X	X
**Primary outcomes**					
Voice quality	X			X	X
Vocal response	X			X	X
ERP	X			X	X
**Secondary outcomes**					
MDS-UPDRS-III	X			X	X
SCWT	X			X	X
QoL	X			X	X
fMRI scanning	X			X	X
**Safety**			X	X	X

### Primary outcomes

#### Voice quality

Participants will perform an array of speech tasks designed to assess various aspects of their speech functions. These tasks consist of sustained vowel phonation, reading a specified passage (Chinese version of “The North Wind and the Sun” that was developed by the International Phonetic Association), spontaneous speech production, a pitch range task that involves gliding the voice from the lowest to the highest pitch and vice versa, as well as a diadochokinetic task that requires rapid and alternative articulatory movements (“pa-tak-ka”). Vocal sound pressure level (SPL), voice *f*_o_, maximum phonation time (MPT), and formant frequencies will be analyzed for sustained vowel phonation. Vocal SPL, speech rate, and syllable repetition rate will be analyzed for speech tasks.

In addition, perceptual voice quality will be assessed using the Japanese GRBAS scale that consists of 5 items: grade, rough, breathiness, asthenia and strain (Moro-Velazquez et al., 2021). To minimize inter-rater variability and enhance reliability of this perceptual evaluation, we will involve three experienced raters, each skilled in evaluating speech disorders associated with PD, to independently assess the speech samples using the GRBAS scale. These raters independently evaluate all speech samples, and their scores are averaged to obtain the final GRBAS ratings. All raters will undergo an alignment process to standardize scoring methods and criteria prior to the start of the study. Furthermore, intra-class correlation coefficients (ICCs) will be calculated to quantitatively measure inter-rater reliability and control for any potential variability.

#### Neurobehavioral changes of vocal motor control

The FAF paradigm will be used to measure neurobehavioral changes in auditory-vocal integration in patients with PD before and after TMS intervention, which will reflect their ability to integrate auditory feedback and motor control for speech processing. They will be instructed to produce sustained phonations while exposed to unexpected pitch perturbations in auditory feedback, with vocal and electroencephalographic (EEG) signals recorded simultaneously (see details below). The magnitude and latency of vocal responses will be measured as behavioral responses, while the P1, N1, and P2 components of the event-related potentials (ERPs) will be measured as neurophysiological responses.

### Secondary outcomes

#### Cognitive function

As a secondary outcome, cognitive function will be assessed using a neuropsychological test that measures attentional control and executive functions. It is noteworthy that emerging research over recent years has progressively expanded our understanding of cerebellar function from motor control to cognitive processes, including but not limited to attentional control (Esterman et al., 2017), working memory (Marvel and Desmond, 2010), and affective regulation (Schmahmann and Sherman, 1998). Specifically, auditory-motor integration for speech production has been shown to bear significant associations with attentional control (Liu et al., 2015), working memory (Guo et al., 2017), and executive function (Ranasinghe et al., 2017). This relationship is further supported by recent studies that provide causal evidence supporting the notion that a top-down neural mechanism mediated by the prefrontal cortex exerts an inhibitory control over auditory-motor processing of speech production (Liu et al., 2020; Chang et al., 2023). It is thus plausible that cTBS over the right cerebellum may yield improvements in both speech production and cognitive function in patients with PD, which will provide insights into the contributions of neurocognitive functions to speech production. To address this point, the Stroop Color and Word Test (SCWT) will be used to assess the ability of attentional control and executive function (Hsieh et al., 2008), during which participants will be asked to name the ink colors of color words printed in discordant ink. The Stroop effect will be calculated as the delay in reaction time between automatic and controlled processing of information.

#### Quality of life

The Parkinson’s Disease Questionnaire (PDQ-39) will be used as a secondary outcome to evaluate the impact of PD on quality of life. It assesses the frequency of difficulties experienced by patients with PD across 8 dimensions of daily living, including relationships, social situations, communication, functioning, and wellbeing. In addition, the Voice Handicap Index (VHI) will be used to evaluate voice-related quality of life.

### Resting-state fMRI

To gain further insight into the neural mechanisms underlying the effect of cerebellar cTBS on speech impairment in patients with PD, rs-fMRI will be used to investigate differences in neural activity patterns between the two groups. Rs-fMRI has emerged as a valuable tool for monitoring disease progression and treatment outcomes in PD (Baggio et al., 2015). In this protocol, rs-fMRI will be used to detect and assess changes in FC, which reflects the local synchronization of spontaneous neural activity, in patients with PD following cerebellar cTBS interventions.

### Data collection and processing

#### Demographic data collection

Demographic information, including age, gender, educational level, hearing function, disease stage, cognitive function, medical history, medication list, and comorbidities, will be collected from all participants. This information will be documented in paper forms and subsequently transferred to electronic files. Study assessors will receive thorough training before conducting the assessments to ensure accurate and consistent data collection.

#### Acoustic data acquisition

All patients with PD will perform speech tasks in a sound-attenuated room under following conditions: sustained vowel phonation, reading a specified passage, spontaneous speech production, a pitch range task, and a diadochokinetic task. Voice signals will be collected via a dynamic microphone (DM2200, Takstar Inc., Huizhou, China) at 44 kHz and transmitted to a computer using Praat software (Boersma, 2001). Acoustic parameters, including vocal SPL, voice *f*_o_, MPT, formant frequencies, speech rate, and syllable repetition rate (Ramig et al., 1996; Wang et al., 2006), will be extracted and analyzed using Praat for statistical analyses.

### Data collection, preprocessing, and analysis

#### Vocal response data

The FAF-based vocal production task will be conducted in a sound-attenuated room. Patients with PD will be instructed to produce sustained phonations of the vowel/u/for approximately 3–4 s at their comfortable pitch and loudness level. During each vocalization, they will hear their voice pitch unexpectedly shifted upward or downward twice by 200 cents (100 cents = 1 semitone), with each perturbation lasting for 200 ms. The first pitch perturbation will occur 900–1,200 ms after the vocal onset, followed by the second pitch perturbation occurring 1,200–1,500 ms after the first one. All patients with PD will take a pause of 3–4 s between successive vocalizations to avoid vocal fatigue. They will produce 100 consecutive vocalizations, resulting in a total of 100 trials for +200 cents and −200 cents pitch perturbations.

To partially mask airborne and bone-conducted feedback, the recording system will be acoustically calibrated so that participants hear voice feedback with a gain of 10 dB SPL higher than their vocal output (Behroozmand et al., 2009; Liu et al., 2011). During the experiment, voice signals will be transduced by a dynamic microphone (DM2200, Takstar Inc., Huizhou, China), amplified with a MOTU Ultralite Mk3 Firewire audio interface (Cambridge, MA, USA), and pitch-shifted through an Eventide Eclipse Harmonizer (Little Ferry, NJ, USA). A custom-developed MIDI software program (Max/MSP v.6.1 by Cycling 74, San Francisco, CA, USA) will control the Eventide Eclipse Harmonizer to shift voice pitch and generate transistor-transistor logic (TTL) control pulses to mark the onset of the pitch perturbation. The pitch-shifted voice signals will be further amplified by an ICON Neo Amp headphone amplifier (Middleton, WI, USA) and delivered to participants through insert earphones (ER-1, Etymotic Research Inc., Elk Grove Village, IL, USA). The original and pitch-shifted voice signals, as well as TTL pulses, will be recorded at 10 kHz by a PowerLab A/D converter (model ML880, AD Instruments, Castle Hill, NSW, Australia) using LabChart software (v.7.0, AD Instruments).

The magnitude and latency of vocal responses to pitch perturbations will be measured using a custom-developed IGO RPRO software program (v.6.0 by WaveMetrics Inc., Lake Oswego, OR, USA) (Liu et al., 2012; Li et al., 2021). Voice *f*_o_ contours in hertz will be extracted from voice signals using Praat software and converted to the cent scale using the formula: cents = 100 × [12 × log2(*f*_o_/reference)] [reference = 195.997 Hz (G3)]. Voice *f*_o_ contours will be segmented into epochs ranging from 200 ms before to 700 ms after the onset of the pitch perturbation and visually inspected to identify and reject any artifacts. Individual trials contaminated by unexpected vocal interruptions or signal processing errors will be regarded as bad trials and excluded from subsequent analyses. Trials without artifacts will be averaged to generate an overall response for each condition. The magnitude and latency of a vocal response will be, respectively measured as the maximum or minimum value in cents and the corresponding time in milliseconds when the voice *f*_o_ contour reaches its peak value.

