#### EEG data

EEG data will be recorded using a 64-electrode Geodesic Sensor Net (Electrical Geodesics Inc., Eugene, OR, USA) connected to a high input-impedance Net Amps 400 amplifier (Electrical Geodesics Inc., Eugene, OR, USA). The EEG signals will be referenced to the vertex (Cz) and digitally sampled at 1 kHz using NetStation software (v.5.4, Electrical Geodesics Inc., Eugene, OR, USA). TTL pulses will be sent to the EEG recording system via an experimental synch Deutsches Institut für Normung (DIN) for synchronization of voice and EEG signals. The impedance levels of individual sensors will be kept below 50 kΩ throughout the recording, as this amplifier accepts scalp-electrode impedances up to 60 kΩ (Ferree et al., 2001).

The EEG signals will be analyzed offline using NetStation software. They will be band-pass filtered with cut-off frequencies of 1–20 Hz and segmented into epochs ranging from 200 ms before to 500 ms after perturbation onset. An artifact detection procedure will be applied to identify bad trials, during which trials whose voltage values exceed ± 55 μv of the moving average over an 80-ms window will be rejected from further analysis. After re-referencing to the average of the electrodes on each mastoid, artifact-free trials will be averaged and baseline-corrected (−200 ms to 0) to generate an overall ERP response for each condition. A total of 24 electrodes in three regions of interest (ROIs) will be selected for statistical analysis (Dai et al., 2022; Lin et al., 2022): frontal area, including AF3, AFz, AF4, F5, F3, F1, Fz, F2, F4, and F6; fronto-central area, including FC5, FC3, FC1, FCz, FC2, FC4, and FC6; and central area, including C5, C3, C1, Cz, C2, C4, and C6. The amplitudes and latencies of the P1, N1 and P2 components will be extracted from the averaged ERPs for each ROI.

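### As written, the vocal response magnitude is an extreme in cents relative to a fixed 195.997 Hz, with no pre-perturbation reference and no post-onset search window, so between-visit pitch drift enters a primary outcome

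*Protocol article*

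**What the plan says.** Vocal response is listed among the primary outcomes in Table 1, and the section on neurobehavioral changes of vocal motor control states: "The magnitude and latency of vocal responses will be measured as behavioral responses".

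The Vocal response data section sets out the processing in order:

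- Pitch in hertz is converted to cents with one fixed reference, 195.997 Hz (G3), for every participant and visit.
- Epochs are cut: "contours will be segmented into epochs ranging from 200 ms before to 700 ms after the onset of the pitch perturbation".
- Bad trials are rejected, and then: "Trials without artifacts will be averaged to generate an overall response for each condition".
- The score is taken: "The magnitude and latency of a vocal response will be, respectively measured as the maximum or minimum value in cents". Latency is the time at which the contour reaches its peak.

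On the tool, the same section says: "The magnitude and latency of vocal responses to pitch perturbations will be measured using a custom-developed IGO RPRO software program". It cites two earlier studies there.

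The EEG data section handles the simultaneous recording differently: "artifact-free trials will be averaged and baseline-corrected". It gives the baseline interval as -200 ms to 0.

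Participants choose their own comfortable pitch in this task. The Statistical analysis section uses a 2 × 3 repeated-measures ANOVA of group by time.

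**The concern.** The construct is compensation: how far the voice moves when its feedback is shifted. The Discussion expects this movement to become smaller after cTBS. To isolate it, the pitch just before the shift has to be removed. The written sequence never removes it. The cents are tied to a musical note, not to the speaker's own pre-shift level, so the extreme of the contour carries the speaker's habitual pitch on that day as well as the response.

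Pitch is free to change between visits. Voice fundamental frequency is itself a primary voice-quality measure, and treatment might alter it. If real and sham stimulation changed habitual pitch differently, that difference would be read as a change in compensation. If drift were merely random, it would add noise to the contrast.

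Two smaller gaps sit in the same definition. The epoch includes 200 ms before onset and no search window is stated, so the extreme and its latency could fall before the perturbation. Maximum or minimum is also not tied to the direction of the shift, although both +200 and -200 cents are used and the ANOVA has no direction factor.

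**Working it through.** **Inputs from the Protocol article.** Cents = 100 × 12 × log2(f/195.997) = 1200 × log2(f/195.997). Epoch -200 to +700 ms. Perturbations of +200 and -200 cents. 20 participants per group. The reference itself checks: G3 lies 14 semitones below 440 Hz, and 440 × 2^(-14/12) = 195.998 Hz.

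**Inputs that are assumptions.** The habitual pitches, the 20-cent response, the sizes of drift and the standard deviations below are illustrative. The documents give none of them.

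**Step 1: what the written score contains.** Let H be habitual pitch in cents relative to 195.997 Hz and R the response. The literal score is Y = H + R; the score relative to the pre-onset mean is Y - H = R. For an assumed upward response of 20 cents:

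| Habitual pitch (Hz) | H (cents) | Score as written | Score relative to baseline |
|---|---|---|---|
| 120 | -849.4 | -829.4 | 20.0 |
| 180 | -147.4 | -127.4 | 20.0 |
| 200 | 35.0 | 55.0 | 20.0 |
| 220 | 200.0 | 220.0 | 20.0 |

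**Step 2: what survives in the planned analysis.** For the change from T0 to T1, ΔY = ΔH + ΔR. The group-by-time contrast is therefore

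(mean ΔR in EG - mean ΔR in CG) + (mean ΔH in EG - mean ΔH in CG).

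The level of H drops out, so the large spread down the table does not bias the comparison. A shift in H common to both arms also drops out. What remains is random drift, which adds variance, and drift that differs between arms, which adds bias.

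**Step 3: size of the drift term.** A proportional change p in habitual pitch moves Y by 1200 × log2(1 + p), whatever the starting pitch:

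- 0.5%: 8.6 cents
- 1%: 17.2 cents
- 2%: 34.3 cents
- 5%: 84.5 cents

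Against the assumed 20-cent response, a 1% drift is 17.2/20 = 86% of the quantity being measured.

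**Step 4: illustrative effect on precision.** Assume a true group difference in change of 10 cents, an SD of change in R of 8 cents, and drift independent of R. With 20 per arm, a two-sided 5% level and a normal approximation, power = Φ(10/SE - 1.96), where SE = SD × √(2/20).

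- Relative to baseline: SD = 8, SE = 2.53, power 0.98.
- As written, drift SD 10 cents: SD = √(64 + 100) = 12.8, SE = 4.05, power 0.69.
- As written, drift SD 30 cents: SD = √(64 + 900) = 31.0, SE = 9.82, power 0.17.

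**Step 5: search window and sign.** The pre-onset part is 200 of 900 ms, or 22% of the epoch over which the extreme could be sought. On sign, suppose equal 20-cent movements occur up in one shift condition and down in the other, and the two signed scores are pooled. Then ((H + 20) + (H - 20))/2 = H and the response disappears. The plan does not say that it pools them; the example only shows why a convention is needed.

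**The case against.** The strongest reply is that an unwritten step is not an excluded step. The section speaks of responses to perturbations, keeps 200 ms before onset for which no other use is stated, and relies on a custom program and two cited studies that are not shown here. A journal article may leave a routine processing step to the full protocol. This stands as evidence of intent, and it is why the point concerns a definition to be corrected and not an invalid outcome. It does not dispose of the point. The article is not silent on the reference: it names 195.997 Hz and then gives a complete definition of the score in cents. At the same level of detail, the EEG section does state its baseline.

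A reader might infer more than the documents support:

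- That the measure would be habitual pitch instead of compensation. Even read literally it is the sum of the two.
- That pitch differences between men and women bias the comparison. Stable differences cancel in the group-by-time contrast, and randomization is stratified by gender.
- That speech therapy alone would create a false effect. Both arms receive it, so a common pitch change cancels.
- That the sample size rests on this measure. The Sample size section takes a partial η² from a study of auditory-vocal integration and does not name the variable behind it.
- That only responses opposing the shift should count. The documents do not settle this, and the point does not require it.

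It is also fair to say that a response latency implies a peak after onset, and that maximum and minimum can be read as upward and downward peaks. Both readings are natural, but neither is written.

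**Conclusion.** The point holds as a fault in a stated definition of a primary outcome. Followed to the letter, the score is habitual pitch plus response, sought over an epoch that includes time before the perturbation. The harm in the planned analysis is confined to between-visit changes in self-chosen pitch that are random or differ between arms. Each 1% of such drift moves the score by about 17 cents. Whether drift of that size occurs in these patients cannot be told from the documents, and the power figures rest wholly on assumed standard deviations. The text suggests that the team means to reference the baseline; if the program already does so, the results are unaffected by this gap and only the description is wrong.

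**What to change.** Amend the Vocal response data section to state that:

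- each epoch is expressed relative to its own mean over -200 to 0 ms;
- magnitude is the peak deviation from that baseline within a fixed, stated post-onset window;
- latency is the time of that peak;
- one pre-specified sign convention for each shift direction is applied identically at T0, T1 and T2.

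The choice of window and of sign convention, including how responses that follow the shift are scored, is for the team to set before unblinding. The 195.997 Hz conversion can stay, because a fixed reference cancels once the baseline is subtracted.

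The cost is one paragraph and a check that the program does what the paragraph says. The pre-onset segment is already recorded, so no new data are needed and the stated sample size does not change.
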